#### Objective 3: interactions among lifestyle change

Outcome interactions, and determinants of such, will be investigated in an exploratory analysis. For instance, those who quit smoking may also be more likely to reduce their alcohol consumption, and this interaction may be moderated by baseline characteristics. In addition, we will investigate interactions between changes in stress and behaviour change. Models to detect such interactions will be explored and findings will be used to create hypotheses for future research.

### Sample size, effect, harm and futility

The trial will use a Bayesian group sequential design^48–50^ to monitor recruitment with interim analyses planned for every 50 participants completing the 4-month follow-up. Each of the primary outcomes will be modelled according to the analysis plan (see Analysis), and coefficients for dummy variables representing presence/absence of each component will be assessed for effect, harm and futility with respect to each outcome. We let ß_k, l, i_ represent the regression coefficient for component *k*, at time l, for outcome *i*, and D all the data currently accumulated, then the target criteria will be:

**Effect (fruit/vegetable and physical activity):** p(ß_k, l, i_ > 0 | D)>97.5% and p(ß_k, l, i_ > 0.10 | D)>50%.
**Harm (fruit/vegetable and physical activity):** p(ß_k, l, i_ < 0 | D)>97.5% and p(ß_k, l, i_ < -0.10 | D)>50%.
**Effect (sugary drinks, alcohol and smoking):** p(ß_k, l, i_ < 0 | D)>97.5% and p(ß_k, l, i_ < -0.10 | D)>50%.
**Harm (sugary drinks, alcohol and smoking):** p(ß_k, l, i_ > 0 | D)>97.5% and p(ß_k, l, i_ > 0.10 | D)>50%.
**Futility (all outcomes):** p(−0.10 < ß_k, l, i_ < 0.10 | D)>95%.

Outcomes analysed using normal regression will be standardised when checking the above criteria. For the effect and harm criteria, we will use a standard normal prior for dummy covariates (mean=0, SD=1.0), and a slightly wider prior will be used for the futility criterion (mean=0, SD=2.0). The criteria should be viewed as targets, thus, at each interim analysis, we will evaluate each criterion and make a decision if we believe that recruitment should stop or continue. We will consider removing factors from the trial if the harm criteria are fulfilled. Note that we are estimating each component’s effect on each outcome, thus we are not a priori excluding any combination. If a component is ineffective with respect to a specific outcome, then this will be captured by the futility criteria, and will also be reported as a finding.

While the final sample size is not determined a priori, we conducted a series of simulations with effect sizes at the minimal value of the above criteria (0.1 Cohen’s d for fruit/vegetable and physical activity, 1.1 incidence rate ratios for sugary drinks and alcohol and 1.1 ORs for smoking). Simulations suggested that approximately 1500–2500 participants will be necessary to recruit. However, the criteria will decide, not the simulations. Recruitment will last no longer than 24 months despite criteria being fulfilled or not. Despite having more conditions than in a traditional two-arm trial (in this case, 64 conditions), the factorial design is fully powered for each contrast.^47^ This can be understood by observing that half the study population are given access to each individual component (see Table 1 in online supplemental appendix 3), thus the other half creates a contrast (a type of control).

Note that the Bayesian approach allows us to make unlimited looks at the data without worrying about multiplicities and error rates, as would be necessary using a frequentist approach.^73^ Also, since no fixed effect size is prespecified, we reduce the risk of stopping recruitment both too early and too late.^50^

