### Aims and objectives

The aim of this study is to estimate the effects of the components of a novel mHealth intervention on multiple lifestyle behaviours (alcohol, diet, physical activity and smoking) among college and university students in Sweden. The study is a part of the Mobile health Multiple Behaviour Interventions across the LifEspan research programme (MoBILE),^46^ which contains seven projects on multiple lifestyle interventions among different populations across the lifespan. The objectives of the study are to:

Estimate the effects of a novel mHealth intervention’s different components on individual lifestyle behaviours:Weekly alcohol consumption and number of episodes per month of heavy drinking.Weekly consumption of sugary drinks and average daily fruit and vegetable consumption.Weekly moderate to vigorous physical activity (MVPA).Four-week point prevalence of smoking.Estimate the degree to which the effects of the components are mediated through perceived importance, confidence and know-how.Detect interactions among lifestyle behaviour change, for example, those who stop smoking may also reduce their alcohol consumption, and the degree to which this is moderated by the components of the intervention.

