##### Primary outcome measures

**Alcohol:** weekly alcohol consumption; monthly frequency of heavy episodic drinking.
**Diet:** average daily consumption of fruit and vegetables; weekly consumption of sugary drinks.
**Physical activity:** weekly MVPA.
**Smoking:** 4-week point prevalence of smoking abstinence.

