#### Primary and secondary outcome measures

Weekly alcohol consumption will be assessed by asking participants the number of standard drinks of alcohol they consumed last week (short-term recall method^55^). Frequency of heavy episodic drinking will be assessed by asking participants how many times they have consumed more than 4/5 (female/male) standard drinks of alcohol on one occasion the past month. These two outcomes are both part of the proposed core outcome set for brief alcohol interventions.^56–58^

Diet and physical activity will be measured using a questionnaire based on the previously published questionnaire by the National Board of Health and Welfare in Sweden^59^ and was further modified to also include portion sizes. The consumption of fruit and vegetables will be measured using two questions concerning the number of portions (100 g) of fruit and vegetables (respectively) the participants ate on average per day during the past week. Sugary drink consumption will be measured by a question regarding the number of units (33 cl) of sugary drink participants consumed the past week. MVPA will be estimated by summing responses to two questions regarding the number of minutes spent on moderate and vigorous physical activity, respectively, during the past week.

BMI will be measured by asking participants to report their weight (both weight and height have been reported at baseline, and height is unlikely to have changed significantly and will, thus, only be asked at baseline).

Four-week point prevalence of smoking abstinence (no cigarettes the past week) will be asked as a binary question. This is a suggested measure by the Society of Research on Nicotine and Tobacco.^60^ Participants who have smoked any cigarette the past 4 weeks will be asked for the number of cigarettes smoked the past week.

Perceived stress will be assessed using the short form perceived stress scale.^61^ There may be a risk that participants experience an increased level of stress as they change their behaviours, for instance, many may have used smoking as a destressor. Findings in relation to this outcome may be useful to address such hypotheses in future research.

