### Models

#### Objective 1: primary and secondary outcomes

Analyses of primary outcomes will be conducted among those fulfilling the respective criteria for inclusion at baseline, for example, weekly alcohol consumption will be analysed among those who reported having consumed 10/15 (female/male) or more units of alcohol the past week. BMI, candy/snacks and stress will be analysed among all participants, and number of cigarettes smoked weekly among baseline smokers.

Weekly alcohol consumption, frequency of heavy episodic drinking per month, weekly intake of candy and snacks, number of sugary drinks per week, and cigarettes smoked per week are all count variables that are likely skewed and over dispersed. Therefore, these outcomes will be analysed using negative binomial regression. If found not to be over dispersed, we will consider using normal regression (possibly log-transformed). Average intake of fruit and vegetables per day, MVPA minutes per week, BMI, and stress will be analysed using normal regression (possibly log-transformed). Point prevalence of smoking abstinence will be analysed using logistic regression.

All models will be adjusted for age, gender and mediators at baseline. We will investigate pairwise interactions among components. Effect modification will be explored in all models to assess if any of the baseline characteristics moderate the effects of the components of the intervention.

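### The smoking lines of the Effect and Harm rules are signed for smoking as the event, but the outcome modelled is abstinence, so as written the two labels are swapped

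*Protocol article*

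**What the plan says.** All places are in the Protocol article.

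- **Primary outcome measures** lists the smoking outcome as "4-week point prevalence of smoking abstinence".
- **Primary and secondary outcome measures** says how it is collected: "Four-week point prevalence of smoking abstinence (no cigarettes the past week) will be asked as a binary question". The recall window in that sentence is a separate matter. What counts here is that the item is about abstinence.
- **Objective 1: primary and secondary outcomes** gives the model: "Point prevalence of smoking abstinence will be analysed using logistic regression".
- **Sample size, effect, harm and futility** ties the interim rules to those models: "Each of the primary outcomes will be modelled according to the analysis plan (see Analysis". It lets beta "represent the regression coefficient for component" k at time l for outcome i.
- **The same section** sets the signs. Under "Effect (sugary drinks, alcohol and smoking", Effect needs more than 97.5% posterior probability that beta is below 0 and more than 50% that it is below -0.10. Harm is the mirror image above 0 and above 0.10. Fruit/vegetables and physical activity have the opposite signs.
- **The same section** attaches a consequence: "We will consider removing factors from the trial if the harm criteria are fulfilled".
- **Aims and objectives** words the outcome the other way round: "Four-week point prevalence of smoking".

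**The concern.** Abstinence is an outcome for which higher is better. In a logistic model of abstinence, a component that helps people quit has a positive coefficient. The rules put smoking among the outcomes for which lower is better, so the printed sign of benefit is opposite to the sign that the printed model gives.

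The rules are checked after every 50 participants who complete the 4-month follow-up. They guide whether recruitment continues and whether a component stays in the trial. If they are coded literally, a component that increases quitting would be flagged as harmful and considered for removal, and a component that reduces quitting would be flagged as effective. Smoking is one of the four target behaviours and a primary outcome.

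**Working it through.** The point concerns a sign, so it does not depend on the projected 1500-2500 participants. That range comes from simulations whose base rates and subgroup sizes the article does not give, so it cannot be reproduced here.

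**Step 1: sign of benefit.** Let A = 1 for abstinent. The model is logit P(A = 1) = a + beta_A × component, with other terms omitted. More quitting in those given the component means beta_A > 0. Let S = 1 - A, so that smoking is the event. Then logit P(S = 1) = -logit P(A = 1), hence beta_S = -beta_A, and benefit means beta_S < 0. The printed smoking rules (Effect below 0, Harm above 0) therefore fit beta_S. The outcome definition and model describe beta_A.

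**Step 2: worked case with the stated prior.** The Normal(0, 1) prior is from the article. These inputs are illustrative assumptions: 200 baseline smokers at each level of a component, with abstinence 20% without it and 35% with it.

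- Log odds ratio for abstinence: ln(0.35/0.65) - ln(0.20/0.80) = 0.767
- Variance: 1/(200 × 0.20 × 0.80) + 1/(200 × 0.35 × 0.65) = 0.03125 + 0.02198 = 0.0532
- Posterior variance with the prior: 1/(1/0.0532 + 1) = 0.0505, so SD 0.225
- Posterior mean: 0.0505 × 0.767/0.0532 = 0.728
- P(beta > 0) = 0.9994 and P(beta > 0.10) = 0.997

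| Component | Event modelled | Posterior mean | Effect as printed | Harm as printed |
|---|---|---|---|---|
| Helps quitting (20% to 35%) | abstinence | +0.728 | not met | met |
| Helps quitting | smoking | -0.728 | met | not met |
| Hinders quitting (35% to 20%) | abstinence | -0.728 | met | not met |
| Hinders quitting | smoking | +0.728 | not met | met |

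**Step 3: how often, in simulation.** This used 5000 runs of a single look, with 200 per level, 20% base abstinence and a component that truly helps.

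| True abstinence OR | Abstinence as event: Effect / Harm | Smoking as event: Effect / Harm |
|---|---|---|
| 1.5 | 0% / 37% | 37% / 0.02% |
| 2.0 | 0% / 84% | 84% / 0% |

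The percentages depend on the assumed rates. The swap does not, because the thresholds are mirror images and the prior on the component coefficients is centred on 0. The simulation shows what each coding implies, not which coding the trial uses.

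**Step 4: extent.** 6 components × 2 time points (2 and 4 months) = 12 smoking coefficients, each assessed for both Effect and Harm. The futility rule, from -0.10 to 0.10 with a prior also centred on 0, gives the same answer for beta_A and -beta_A.

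**The case against.** The strongest reply is that the article never says which level of the binary outcome is coded 1. A model for abstinence and one for its complement are the same model with the sign reversed. The rule lines say smoking rather than abstinence, the objectives speak of the prevalence of smoking, and under that coding every printed sign is right. Smoking as the event may well have been intended, and the coding may be fixed in an analysis plan or program that is not shown. This stands to the extent that the swap is conditional on abstinence being the modelled event. It does not remove the conflict. The outcome list, the measurement text and the model all name abstinence, the rules are tied to that model, and nothing says that the indicator is reversed. This is a clash between two printed statements, not a detail left to the analysis plan.

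A second reply is that the criteria are described as targets, that a decision is made at each look, and that removal is only considered. This also stands. Someone may notice that a flagged harm is a rise in quitting. It lessens the likely damage but leaves the written rule as it is.

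Three stronger readings are tempting and not supported:

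- **That every final smoking conclusion would point the wrong way.** The Analysis section reports posterior probabilities, medians and 50% and 95% intervals. These do not pass through the Effect and Harm labels.
- **That recruitment would stop at the wrong time.** Because the rules mirror each other, swapping the labels leaves unchanged the look at which one or other smoking criterion is met.
- **That the simulated odds ratio of 1.1 for smoking proves the error.** The article uses 1.1 for alcohol and sugary drinks too, where benefit is a ratio below 1. The figure gives a size, not a direction.

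**Conclusion.** Wrong as written. Taking the outcome and model as printed, with abstinence as the event, the Effect and Harm labels are reversed for all 12 smoking coefficients at every interim look. The practical exposure is a component that helps quitting being considered for removal, and one that hinders quitting being flagged as effective. If smoking is in fact the modelled event, the signs are right and the fault lies in the outcome and model wording. In either case the article gives two opposite event definitions for a primary outcome whose rule depends on direction. A reader might infer that the interim analyses are actually running with inverted labels. The article does not show the code, so that cannot be concluded.

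**What to change.** Use one event definition in Aims and objectives, Primary outcome measures, Primary and secondary outcome measures, Objective 1, and Sample size, effect, harm and futility. Either of two changes does this:

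1. Keep abstinence as the modelled event and move smoking to the fruit/vegetable and physical activity lines (Effect: beta > 0 and beta > 0.10; Harm: beta < 0 and beta < -0.10).
2. State that the modelled event is smoking in the past 4 weeks and keep the printed signs.

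Then check that the interim-analysis code uses the same event and the same signs. The cost is a few words and a code check. No further data or participants are needed, and the futility rule stays as it is.

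### The simulations behind 1500–2500 participants place the true effect on the decision cut-off, where a single analysis meets the effect rule at most about half the time, so the range does not support the stated power claims

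*Protocol article*

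**What the plan says.** All of this is in the protocol article; the rules and the simulations are in the section on sample size, effect, harm and futility.

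- **Effect rule.** Under "Effect (fruit/vegetable and physical activity" the rule is "p(ß_k, l, i_ > 0 | D)>97.5% and p(ß_k, l, i_ > 0.10 | D)>50" per cent. For sugary drinks, alcohol and smoking it is the mirror image: "p(ß_k, l, i_ < 0 | D)>97.5% and p(ß_k, l, i_ < -0.10 | D)>50" per cent.
- **Futility rule, all outcomes.** "p(−0.10 < ß_k, l, i_ < 0.10 | D)>95" per cent.
- **Priors.** For effect and harm, "we will use a standard normal prior for dummy covariates (mean=0, SD=1.0"); for futility, "a slightly wider prior will be used for the futility criterion (mean=0, SD=2.0").
- **Looks.** One for every 50 participants who complete the 4-month follow-up. The criteria are described as targets for a judgement on stopping.
- **Simulations.** "we conducted a series of simulations with effect sizes at the minimal value of the above criteria": Cohen's d of 0.1 for fruit/vegetables and physical activity, and "1.1 incidence rate ratios for sugary drinks and alcohol and 1.1 ORs for smoking". They lead to roughly 1500–2500 participants. The text adds that the criteria, not the simulations, settle the final number, and that recruitment ends by 24 months whether or not criteria are met.
- **Claims.** The Abstract presents 1500–2500 as the number needed. The strengths and limitations list says the sequential design ensures the trial will not be underpowered. The sample size section calls the factorial design fully powered for each contrast.
- **Analysis sets.** Under Objective 1, each primary outcome is analysed only among participants who met that outcome's inclusion criterion at baseline.

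**The concern.** The second half of the effect rule is a condition on the posterior median: it must lie beyond 0.10. The simulations set the true effect at that same 0.10. When the truth sits on the cut-off, the median falls on the favourable side about half the time, and recruiting more people does not change that. A simulation placed there cannot show that the trial would reliably detect an effect worth having.

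This is the only numerical basis given for the sample size, and the protocol attaches no probability of effect, harm, futility or no decision to it. A reader of the Abstract will take 1500–2500 as the size at which the trial can be expected to answer its questions. Because recruitment stops at 24 months regardless, the trial could end near that size with several component-by-outcome questions undecided.

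**Working it through.** **The plan's own figure.** 1500–2500 cannot be strictly reproduced: the article gives no target probability, SD, event rate, dispersion or dropout for it. What can be checked is how the stated rule behaves at the stated effects.

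**Model (assumed, and favourable to the plan).** One component, one standardised outcome with SD 1, 1:1 contrast, everyone analysable, criteria applied strictly. Then SE = 2/√N. With the N(0, 1) prior, posterior mean = w × estimate, where w = 1/(1 + SE²), and posterior SD = SE/√(1 + SE²). The effect rule is met when the posterior mean exceeds the larger of 0.10 and 1.96 × posterior SD. So

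P(rule met) = 1 − Φ((c − β)/SE), with c = max(0.10, 1.96 × posterior SD)/w.

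**Single analysis, β = 0.10.**
- N = 1500: SE = 0.0516, 1.96 × posterior SD = 0.1011, w = 0.9973, c = 0.1013. (0.1013 − 0.10)/0.0516 = 0.025, so P = 49.0%.
- N = 2500: SE = 0.04, 1.96 × 0.04 = 0.078 < 0.10, so the median condition governs; w = 0.9984, c = 0.1002. P = 49.8%.
- N = 100,000: P = 50.0%.

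The two conditions coincide where 1.96 × 2/√N = 0.10, that is N = 39.2² = 1537. Beyond that the median condition is the binding one.

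**Single analysis, ratio of 1.1 taken as exact.** ln(1.1) = 0.0953, against exp(0.10) = 1.105 and exp(−0.10) = 0.905. In the same model:

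| True β | N = 1500 | N = 2500 | N = 10,000 | N = 100,000 |
|---|---|---|---|---|
| 0.0953 | 45.3% | 45.2% | 40.7% | 22.9% |
| 0.10 | 49.0% | 49.8% | 49.9% | 50.0% |
| 0.15 (illustrative) | 82.7% | 89.4% | 99.4% | 100% |
| 0.20 (illustrative) | 97.2% | 99.4% | 100% | 100% |

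**Sequential looks.** 20,000 simulated trials, looks every 50, chance that the effect rule has been met at least once:

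| True β | by 1500 | by 2500 |
|---|---|---|
| 0 | 12.9% | 13.7% |
| 0.0953 | 63.7% | 73.8% |
| 0.10 | 66.5% | 76.5% |
| 0.15 | 90.2% | 96.6% |

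If looks start only at 500, a true 0.10 gives 62.6% and 73.9%, and a true 0 gives 8.0% and 8.9%. The rise above 50% at β = 0.10 comes partly from early random highs, as the row for a true effect of zero shows.

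**Where a range like 1500–2500 could come from.** With the N(0, 2²) prior and an estimate of exactly zero, the posterior probability inside ±0.10 is 94.7% at N = 1500 and 95.1% at 1550, so futility cannot be declared before about 1550. Under β = 0 it has been met in 54% of trials by 2000 and 73% by 2500. The first stop for any criterion has 50th and 80th percentiles of 1700 and 2250 under β = 0, and 900 and 2000 under β = 0.10.

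**At-risk subsets: smoking as the example.** The Introduction gives 17% smokers among 18–29-year-olds. If that held in the trial (assumption), smokers would number 0.17 × 1500 = 255 to 0.17 × 2500 = 425. Assume 20% or 30% abstinent and SE = 2/√(n p(1 − p)).
- n = 425, p = 0.20: SE = 2/√68 = 0.2425, posterior SD 0.2357, w = 0.9445, c = 1.96 × 0.2357/0.9445 = 0.489. (0.489 − 0.0953)/0.2425 = 1.62, so P ≈ 5%.
- n = 425, p = 0.30: P ≈ 6%.
- n ≈ 250: P ≈ 4% (p = 0.20) and 5% (p = 0.30).

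**The case against.** The best defence is that 1500–2500 was never a power calculation. The text says the final size is not fixed in advance and that the criteria decide. Read as a projected stopping range, simulating near the boundary is a cautious choice, because larger effects tend to stop sooner. The stopping percentiles above fit that reading, especially through futility. This stands as a possible reading, but the article neither states it nor says which criterion drives the range, while the Abstract and the strengths list use the figure and the design as assurance of adequate size.

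Three further points have weight.
- The statement about full power for each contrast is explained by half the sample receiving each component. It is a claim about factorial efficiency, not about the simulation.
- 1.1 may simply be 1.105 rounded. If so, the fall in success with growing N does not arise; at the planned sizes the difference is small either way (about 45% against 49–50%).
- A ratio of 1.1 for drinks and alcohol lies on the harm side as written, but the rules and prior are symmetric, so the numbers do not change.

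An article may leave full operating characteristics to another document. The point here is different: the article itself states the simulated effects, the rule and the resulting size, and they do not fit the assurance drawn from them.

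**Conclusion.** The point holds in limited form. Any single analysis, the last one included, meets the effect rule at most about half the time when the truth is at the simulated value. Under the planned looks, the chance of meeting it at some look is about 67% by 1500 and 77% by 2500. Neither figure supports an assurance that the trial will not be underpowered, and the 24-month limit removes the option of recruiting until a criterion is met.

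A reader might infer more than the document supports.
- It does not follow that the whole design is capped at 50%: the cap is per analysis.
- It does not follow that 1500–2500 is meaningless: it can be a projected stopping range.
- Nor can one say that stopped trials will overstate the effect by some fixed multiple. That depends on mandatory stopping from the very first looks, whereas the criteria are targets for judgement.

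The half-chance result follows from the rule alone. The other percentages rest on a unit-SD normal outcome, full follow-up, one contrast and strict application of the criteria. Subset outcomes will do worse; the 4–6% for smoking rests on the assumed 17% prevalence and 20–30% abstinence. Whether the authors' simulations allowed for subsets is not stated.

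**What to change.** Re-run the simulations at β = 0, at the threshold, and at effects clear of it (0.15 and 0.20 would serve as illustrations), in the benefit direction on the log scale for ratio outcomes, with the expected at-risk subset size for each outcome. Then:

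- restate 1500–2500 with the probabilities of effect, harm, futility and no decision at each size;
- say plainly that, for a true effect at the threshold, a single analysis succeeds about half the time;
- give the ratio thresholds as exp(±0.10), that is 1.105 and 0.905;
- qualify the statement that the trial will not be underpowered and the Abstract's wording on the number needed, given the 24-month limit.

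The cost is analyst time, revised wording and probably a less favourable stated figure. Trial conduct does not change.

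### The claim that unlimited looks need no concern for error rates does not hold for the stated rule: a null coefficient meets the effect or harm target at some look in about 27 to 29% of trials

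*Protocol article*

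**What the plan says.** All of this stands in the protocol article, section Sample size, effect, harm and futility, unless noted.

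- Looks: "interim analyses planned for every 50 participants completing the 4-month follow-up". With the anticipated 1,500 to 2,500 participants, that is 30 to 50 looks.
- Effect target: posterior probability above 97.5% that the coefficient has the favourable sign, and above 50% that it lies beyond 0.10. Harm is the mirror image. Futility requires more than 95% probability of lying within ±0.10.
- Priors: normal with mean 0, SD 1.0 for effect and harm, SD 2.0 for futility. "Outcomes analysed using normal regression will be standardised when checking the above criteria".
- Use: the criteria are called targets, and a decision is made at each look. "We will consider removing factors from the trial if the harm criteria are fulfilled".
- Planning effects: Cohen's d 0.1, incidence rate ratio 1.1, odds ratio 1.1.
- Justification: "the Bayesian approach allows us to make unlimited looks at the data without worrying about multiplicities and error rates". The next sentence adds that having no prespecified effect size reduces the risk of stopping too early or too late.
- The Analysis section makes the posterior median the point estimate.

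**The concern.** Bayesian inference does not depend on the stopping rule in one specific sense: averaged over true effects drawn from the prior, posterior statements remain correct however often one looks. That guarantee is only as good as the prior. N(0,1) puts 92% of its mass beyond ±0.10, with a median absolute effect of 0.67. On a standardised scale this expects effects far larger than the 0.10 used for planning. For effects of the planned size the prior hardly shrinks anything, and frequent looks act almost like unadjusted repeated testing.

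Two things are at stake. Targets may be met by noise, most often early, when the team must decide whether to continue or to remove a factor. If a decision is taken there, the estimate at that point is too large and its posterior probability too confident. This is a failure of calibration in Bayesian terms. It does not depend on requiring frequentist type I error control.

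**Working it through.** **The plan's own figure.** Since "half the study population are given access to each individual component", a present/absent contrast on a standardised outcome has SE = 2/√n. For d = 0.10 the 97.5% limb has 50% power when 0.10 = 1.96 × 2/√n, so n = 4 × 19.6² ≈ 1,537. Power is 49% at 1,500 (0.10/0.0516 = 1.94) and 70.5% at 2,500 (0.10/0.04 = 2.5). The range 1,500 to 2,500 is therefore plausible. It cannot be reproduced exactly, because no target probability is stated. The simulations are described only at the minimal effect.

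**Rule in formulas.** Information is I = n/(4v), with v = 1 for a standardised outcome. With the N(0,1) prior, the posterior mean is m = S/(I+1), where S is the accumulated score, and the posterior SD is s = 1/√(I+1). Effect is met when m > 1.96s and m > 0.10; harm is the mirror image.

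| Completers | I | Share of raw estimate kept, I/(I+1) | Smallest m that meets effect |
|---|---|---|---|
| 50 | 12.5 | 0.926 | 0.53 |
| 300 | 75 | 0.987 | 0.22 |
| 1,500 | 375 | 0.997 | 0.10 |

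The prior removes about 7% of the raw estimate at the first look and about 1% at 300. Any coefficient flagged at 300 must have an estimate of at least 0.22.

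Futility cannot act as an early brake. It needs s < 0.10/1.96 = 0.051, that is about 1,540 completers in the full sample.

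**Null coefficient, simulated** (40,000 runs, looks every 50, normal approximation):

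- Effect or harm met at some look: 27.0% to 1,500 and 28.5% to 2,500, half in each direction. About 18% is reached by 500 completers.
- At a single look: 5.0% at 1,500 and 1.2% at 2,500.
- An individual-level check (600 trials, 64 conditions, all six dummies fitted jointly, outcome re-standardised at each look) gives 27.3% and 29.4%.
- Smoking: about 18%, assuming that 17% of participants smoke at baseline (the survey figure in the Introduction) and 20% are abstinent at follow-up, so v = 1/(0.2 × 0.8) = 6.25.
- First look moved to 100, 200, 500 or 1,000: about 27%, 24%, 19% and 12.8%.

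**Estimate at the first effect flag, looks to 2,500, full sample:**

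- True 0.10: mean about 0.22 (2.2-fold), median about 0.17 (1.7-fold).
- True 0.20: mean about 1.5-fold, median about 1.25-fold.

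**Calibration check.** If true effects are drawn from N(0,1), flagged estimates average 0.835 against a true mean of 0.836, so the method is sound when the prior is right. If they are drawn from N(0, 0.1²), flagged estimates average 0.254 against a true mean of 0.098. The same coefficients followed to 2,500 average 0.114. With N(0, 0.2²) the figures at first flag are 0.31 against 0.19. The spread of true effects is an assumption in each case.

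**The case against.** The strongest reply is that the criteria are targets. No crossing of one coefficient stops the trial, and removal of a factor is only to be considered. This stands. The 27 to 29% is the chance of ever crossing, not of a false stop or a false final result. Of the null coefficients that ever crossed, only about 4% are still flagged at 2,500.

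A reader might infer that more than a quarter of null components would wrongly stop recruitment or be dropped, or multiply the rate over six components into a near-certain false decision. The document does not support that: it describes a judgement at trial level, which none of these calculations models.

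A reader might also infer that flagged effects are generally overstated two- to four-fold or more. That needs the estimate to be frozen at the first flag and, in the full sample, true effects of about 0.10 or less. Larger factors arise in small outcome subsets, but they rest on subset shares from a general survey of 18 to 29 year-olds, not from trial participants.

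Nor does the first look lack usable data because 50 completers face 64 conditions. Each component contrast is about 25 against 25.

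Finally, 0.10 is the minimal value in the criteria, not a claim about likely effects, so the true effects could be larger. If they were spread like N(0,1), the sentence would be right. Nothing in the document argues for effects of that size.

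**Conclusion.** The concern holds in a bounded form. The sentence claims freedom from error-rate concerns that the rule does not have. Per null full-sample coefficient, the effect or harm target is met at some look in about 27% (to 1,500) to 29% (to 2,500) of trials, and in about 18% for smoking under the stated assumptions. At a true effect of 0.10 the mean first-flag estimate is about 2.2 times the truth. Non-binding targets limit the harm to results where recruitment stops, or a factor is removed, at or near a flag. They do not make the statement correct, because a judgement made at each look needs calibrated inputs.

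The figures assume a normal approximation with independent increments, residual SD 1, 1:1 allocation per component and a look at every 50 completers.

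**What to change.** 1. Replace the sentence on unlimited looks with the simulated false-trigger and overestimation rates of the rule, under null and small effects as well as at the minimal effect.
2. State a minimum number of completers, overall and per outcome subset, before the effect and harm targets are acted on. As an example, 1,000 overall with the existing prior lowers the null trigger from 28.5% to 12.8% and the mean first-flag estimate at a true 0.10 from 0.22 to 0.14. Detection of a true 0.10 falls from 76% to 72%. This concerns the posterior targets as triggers only, not removal of a component for other reasons.
3. Report flagged coefficients again under a more sceptical prior chosen for each outcome scale, as a sensitivity analysis.

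A single tight prior such as N(0, 0.1²) should not be imposed on all outcomes. Under the smoking assumptions above, a true log odds ratio of 0.5 would be flagged in only about 0.2% of trials, against 67% under the present rule.

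The cost is wording and simulation time. The real downside is delay: with a minimum of 1,000, a true 0.20 is first flagged at 1,000 completers rather than at a median of about 300.
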